### Secondary endpoint

The secondary endpoints include intraoperative outcomes, postoperative recovery, postoperative pain assessment, pathological outcomes, early morbidity and mortality rate, cosmetic effects, quality of life, 3-year overall survival (OS), incidence of incisional hernia, 5-year DFS and 5-year OS. The intraoperative outcomes include operative time, estimated blood loss, complications, incision length, total incision length, and conversion rate measured intraoperatively. The postoperative recovery outcomes include time to first flatus/stool, time to liquid diet and soft diet, and length of theoretical hospital stay measured upon daily visits during hospitalization. To adjust for the potential impact of the nonmedical variables of different centres, a theoretical length of hospital stay will be used, defined as the postoperative day when patients meet the following predefined discharge criteria: no fever; no need for intravenous nutritional support; passage of first flatus/stool; able to leave the bed with limited assistance. The postoperative pain assessment will be measured on postoperative Days 1, 2, and 3, including the postoperative pain score, which will be recorded using the visual analogue scale (VAS) pain score and dosage of postoperative pain killer intake. The pathologic outcomes, including tumour size, number of harvested lymph nodes, proximal and distal resection margins, and mesangial integrity evaluation (rectum), will be determined postoperatively by pathological examination. Early morbidity, graded according to the Clavien–Dindo classification is defined as postoperative complications observed within 30 days after surgery. The cosmetic effect will be measured by a questionnaire at 1, 6, and 12 months postoperatively. Quality of life will be measured using the European Organization for Research and Treatment of Cancer (EORTC) Quality of Life Questionnaire-Core 30 (QLQ-C30) and the EORTC Quality of Life Questionnaire-Colorectal 29 (QLQ-CR29) preoperatively and at 1, 6, and 12 months postoperatively. The incidence of incisional hernia will be measured at 60 months postoperatively. Incisional hernia will be confirmed by physical examination or radiological methods. Other long-term outcomes include 3-year overall survival (OS), 5-year DFS, and 5-year OS.

### Randomization and blinding

This will be an open-label trial. Surgical procedures and postoperative intervention will not be concealed from patients or investigators. The participants will be randomly assigned to either the CLS or SILS group at a 1:1 ratio using a central, dynamic, and stratified block randomization method. The control factors include age, preoperative stage, and planned surgical intervention. An investigator from each centre will fill in the information of every participant through the network, and the central random system will analyse the information and give the random number and grouping.

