### Sample size calculation

In this study, the 3-year DFS is the main effectiveness evaluation index for noninferiority evaluation. According to previous studies [27–29], the 3-year DFS of the CLS group was approximately 75%. This study assumes that the 3-year DFS of the study group is the same as that of the control group. The expected enrolment time is 3 years, and the follow-up time to reach the primary endpoint is 3 years. If the acceptable noninferiority limit of DFS in the three years of this study is 10%, when DFS is exponentially distributed, the corresponding HR limit is 1.49. This number will be combined with "Log-Rank Tests for Noninferiority" in the professional sample size estimation software NCSS-PASS (14th edition, NCSS, LLC, Utah, USA). When the unilateral statistical significance level is 0.025, the inspection efficiency is 80%, and the study group and the control group will be allocated in the ratio of 1:1, the required sample size of each group will be 284. Considering that the largest abscission rate in this clinical study is approximately 20%, it was finally determined that the sample size of each group will be 355 cases, and the total number of cases required will be 710.

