### Statistical methods

SAS 9.4 statistical software will be used to perform the statistical analyses. The noninferiority analysis for the primary endpoint of 3-year DFS will be conducted by comparing 95% confidence intervals of survival rates between the test and control groups on a modified intent-to-treat (MITT) population basis. Baseline data and validity analyses will be conducted on a modified intent-to-treat (MITT) basis. The primary endpoint will also be analysed on a per-protocol (PP) basis, with the MITT analysis results prevailing. Safety evaluation, including laboratory test data, will be conducted in the safety analysis population (SAP). There is no planned interim analysis for the 3-year DFS rate. Continuous data will be described as the means with standard deviations or medians with interquartile ranges, and categorical data will be expressed as frequencies and percentages. Comparisons between groups will be conducted using the Wilcoxon rank-sum test, Student’s t test, Pearson χ2 test, and Fisher exact test, as appropriate. Survival data will be analysed using the Kaplan–Meier method and log-rank test. A general linear model for quantitative indicators, logistic regression for qualitative indicators, and Cox's proportional hazards model for survival data will be used to assess the effects of baseline, treatment, centre, and treatment-by-centre interactions. A two-sided *p* value < 0.05 will be considered statistically significant.

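### Allocation is balanced on age, stage and planned operation, but the primary 3-year DFS rate comparison as described does not use these factors, so a small gain in precision is forgone

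*Protocol article*

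**What the plan says.** All references are to the protocol article.

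- **Randomization and blinding:** patients are assigned 1:1 "using a central, dynamic, and stratified block randomization method", and "The control factors include age, preoperative stage, and planned surgical intervention".
- **Statistical methods, primary analysis:** noninferiority is judged by "comparing 95% confidence intervals of survival rates between the test and control groups on a modified intent-to-treat (MITT) population basis". More generally, "Survival data will be analysed using the Kaplan–Meier method and log-rank test". Neither sentence mentions stratification or adjustment.
- **Statistical methods, models:** "Cox's proportional hazards model for survival data will be used to assess the effects of baseline, treatment, centre, and treatment-by-centre interactions". This model is not tied to the noninferiority decision. Its baseline terms are not itemised. It names centre, which is not among the listed allocation factors, and does not name the three that are.
- **Sample size calculation:** "the 3-year DFS of the CLS group was approximately 75" per cent; "This study assumes that the 3-year DFS of the study group is the same as that of the control group"; and "the acceptable noninferiority limit of DFS in the three years of this study is 10" per cent. The size comes from a log-rank noninferiority procedure in which no strata are mentioned.

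**The concern.** When allocation is forced to balance on factors that predict outcome, the two groups differ less by chance than under simple randomisation. A crude standard error for the difference in DFS rates does not know this. It still counts the between-stratum variation that the design has removed, so the interval is wider than it needs to be and the test runs below its nominal error rate.

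In a noninferiority trial the width of the interval decides the result. A trial that balances on stage, and then sets stage aside in the main comparison, gives up precision that it could have for nothing. What is at stake is a modest loss of sharpness, not the validity of a noninferiority claim.

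**Working it through.** **1. The plan's own figure.** Inputs from Sample size calculation: 75% DFS at 3 years in both groups, HR limit 1.49, one-sided 0.025, power 80%, 3 years of accrual plus 3 of follow-up.

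- Events: 4(1.960 + 0.842)² / (ln 1.49)² = 197.4.
- Average event probability, exponential DFS with uniform accrual: λ = −ln(0.75)/3, and 1 − (0.75 − 0.5625)/(3λ) = 0.348.
- Per group: 197.4 / 0.348 / 2 = 283.5, so 284. With 20% dropout, 284/0.80 = 355, total 710.

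The plan's numbers reproduce, and no strata enter them. The 10% limit is read as percentage points: ln(0.65)/ln(0.75) = 1.497, against the stated 1.49.

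**2. Rate scale, unadjusted.** Assume 284 per group with known 36-month status, a true difference of 0, and a decision based on the confidence interval for the difference.

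- SE = √(2 × 0.75 × 0.25 / 284) = 0.0363; half-width 1.96 × SE = 7.12 points.
- Power by the simple formula: Φ(0.10/SE − 1.96) = 78.6%.

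**3. Effect of balancing.** Let R² be the share of outcome variance explained by the factors and k = √(1 − R²). With allocation balanced within strata, the true SE is k × SE, while the crude interval still uses SE. Then:

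- true one-sided error of the crude test = Φ(−1.96/k);
- its true power = Φ((0.10/SE − 1.96)/k);
- half-width after adjustment = 1.96 × k × SE;
- power after adjustment = Φ(0.10/(k × SE) − 1.96).

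The document gives no prognostic strength, so a range is assumed: three strata holding 20%, 40% and 40% of patients, with mean DFS 75%. For the moderate case, between-stratum variance = 0.2 × 0.13² + 0.4 × 0.04² + 0.4 × 0.105² = 0.00843, and R² = 0.00843/0.1875 = 0.045.

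| Assumed DFS by stratum | R² | k | Half-width, crude / adjusted (points) | Crude one-sided error | Crude coverage | Power, crude / adjusted | Gain (points) |
|---|---|---|---|---|---|---|---|
| Weak: 82 / 77 / 69.5% | 0.0125 | 0.994 | 7.12 / 7.08 | 0.024 | 95.1% | 78.7 / 79.1% | 0.4 |
| Moderate: 88 / 79 / 64.5% | 0.045 | 0.977 | 7.12 / 6.96 | 0.022 | 95.5% | 79.1 / 80.4% | 1.3 |
| Strong: 94 / 82 / 58.5% | 0.107 | 0.945 | 7.12 / 6.73 | 0.019 | 96.2% | 79.9 / 83.0% | about 3 |

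**4. Hazard-ratio scale.** Simulation under the same strata: 568 patients, balanced allocation, true HR 1, limit 1.49, 3 + 3 years. Runs: 2,500 for the weak case and 1,000 each for the others.

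| Case | SE of log HR, unstratified / stratified Cox | Power, unstratified / stratified |
|---|---|---|
| Weak | 0.1427 / 0.1429 | 80.3 / 80.2% |
| Moderate | 0.1434 / 0.1436 | 80.3 / 79.3% |
| Strong | 0.1446 / 0.1447 | 79.1 / 78.0% |

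The Monte Carlo error of each power figure is √(0.8 × 0.2/2,500) = 0.8 points for the weak case and √(0.8 × 0.2/1,000) = 1.3 points for the others. Stratifying does not narrow the interval, and no power gain appears.

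**The case against.** The strongest reply is that the article is silent rather than wrong. It nowhere says that the primary comparison will be crude. Details of stratification and covariates commonly sit in the statistical analysis plan, which is not shown, and the planned Cox model has baseline terms that could include all three factors. This stands in part: a reader should not conclude that the trial has committed to an unadjusted analysis. But the article does fix the scale, population and decision tool of the primary analysis, and it separates the Cox model from that decision. The factors are therefore absent where they would matter.

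Four stronger readings are tempting and are not supported.

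- **The planned power is eroded.** It is not. The 80% was computed without strata, and on the rate scale balancing raises the crude test's power from 78.6% to between 78.7% and 79.9%. The gap between 78.6% and 80% comes from sizing on the hazard-ratio scale and deciding on the rate scale, not from leaving out the factors.
- **A false noninferiority claim becomes more likely.** The opposite holds: the error is below 0.025.
- **A stratified Cox model or stratified log-rank test would recover the gain.** At the limit of 1.49 the simulation shows none.
- **The loss is known to be sizeable.** The document gives neither a stage mix nor DFS by stage. With weak factors the gain is under half a point.

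The allocation scheme is called both dynamic and stratified block. These terms usually mean different methods, though a hybrid is possible. The calculation assumes near balance within strata; the wording is a side issue that does not change the direction of the result.

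**Conclusion.** The point holds as a minor one. Allocation uses three factors that the described primary rate comparison does not. If that comparison is run crude, the 95% interval is slightly conservative, and adjustment would shorten its half-width of 7.12 points to between 7.08 and 6.73.

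The direction is firm on the rate scale, provided the factors carry any prognostic information. The size is not firm. It rests on an assumed R² of about 1% to 11%, complete 36-month status in 284 patients per group, equal true DFS, and close balance within strata.

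**What to change.** State that the primary 36-month DFS difference and its 95% confidence interval will be a stratum-weighted Kaplan-Meier difference, or a covariate-standardised one, using the three factors as entered in the central randomisation system.

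- With stratum shares w, the estimate is Σ w(S_SILS − S_CLS) at 36 months, and its variance is the sum of w² times the within-stratum variances. This targets the same population-level difference, so the 10-point margin is unchanged.
- Fix the categories and a rule for pooling sparse strata before outcome data are compared.
- Keep crude curves and rates for display.
- If a stratified log-rank test or Cox model is also reported, do not justify it by a power gain at the limit of 1.49.

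The cost is wording only. The factors are already captured to allocate patients, and neither the sample size nor trial conduct changes. If the statistical analysis plan already says this, a cross-reference is enough.

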### Data management

An electronic data capture (EDC) system designed by the Clinical Research Center, Shanghai Jiao Tong University School of Medicine, will be used for data collection and query handling. The investigators will log into the EDC system via the website and record the data on the electronic case report form (eCRF). The investigators are required to submit the data within 7 days of its generation to ensure the timeliness of the data recorded. The clinical research associates are responsible for verifying the raw data and the eCRF to ensure the authenticity, accuracy and completeness of the data recorded.

### Data monitoring

An Independent Data Monitoring Committee (IDMC) composed of an independent contract research organization (CRO) will be set up to ensure the protection of patients, to ensure the ethical conduct of the study, to ensure the accuracy, completeness, and timeliness of the data, to evaluate the benefit/risk ratio of the study and to ensure an independent review of the scientific outcomes during and at the completion of the study. The committee is independent from the sponsor and has no competing interests. Monitoring will be conducted at each centre on a monthly basis during the enrolment period and every two months during the follow-up period.

### Sample size calculation

In this study, the 3-year DFS is the main effectiveness evaluation index for noninferiority evaluation. According to previous studies [27–29], the 3-year DFS of the CLS group was approximately 75%. This study assumes that the 3-year DFS of the study group is the same as that of the control group. The expected enrolment time is 3 years, and the follow-up time to reach the primary endpoint is 3 years. If the acceptable noninferiority limit of DFS in the three years of this study is 10%, when DFS is exponentially distributed, the corresponding HR limit is 1.49. This number will be combined with "Log-Rank Tests for Noninferiority" in the professional sample size estimation software NCSS-PASS (14th edition, NCSS, LLC, Utah, USA). When the unilateral statistical significance level is 0.025, the inspection efficiency is 80%, and the study group and the control group will be allocated in the ratio of 1:1, the required sample size of each group will be 284. Considering that the largest abscission rate in this clinical study is approximately 20%, it was finally determined that the sample size of each group will be 355 cases, and the total number of cases required will be 710.

### Statistical methods

SAS 9.4 statistical software will be used to perform the statistical analyses. The noninferiority analysis for the primary endpoint of 3-year DFS will be conducted by comparing 95% confidence intervals of survival rates between the test and control groups on a modified intent-to-treat (MITT) population basis. Baseline data and validity analyses will be conducted on a modified intent-to-treat (MITT) basis. The primary endpoint will also be analysed on a per-protocol (PP) basis, with the MITT analysis results prevailing. Safety evaluation, including laboratory test data, will be conducted in the safety analysis population (SAP). There is no planned interim analysis for the 3-year DFS rate. Continuous data will be described as the means with standard deviations or medians with interquartile ranges, and categorical data will be expressed as frequencies and percentages. Comparisons between groups will be conducted using the Wilcoxon rank-sum test, Student’s t test, Pearson χ2 test, and Fisher exact test, as appropriate. Survival data will be analysed using the Kaplan–Meier method and log-rank test. A general linear model for quantitative indicators, logistic regression for qualitative indicators, and Cox's proportional hazards model for survival data will be used to assess the effects of baseline, treatment, centre, and treatment-by-centre interactions. A two-sided *p* value < 0.05 will be considered statistically significant.

### Adverse events

Based on the qualifications of the participating centres and surgeons in this study, treatment-related deaths or life-threatening complications due to surgery are generally unlikely to occur. All adverse events (AEs) will be graded according to the Clavien–Dindo classification or Common Terminology Criteria for Adverse Events (CTCAE) version 5.0 and recorded. Any death or unexpected Grade 4 adverse event will be reported urgently to the principal investigator within 24 h. It will also be reported to the Ethics Committee within 72 h, and a detailed medical report will be generated within 15 days. The CSILS Efficacy and Safety Evaluation Committee will be responsible for assessing the quality of surgery by reviewing surgical videos and monitoring each center’s safety. If treatment-related deaths or life-threatening complications occur in up to 3% of the preallocated proportion of patients at each centre, patient enrolment will be terminated immediately and the Ethics Committee will reassess the safety of the trial.

## Discussion

As an emerging minimally invasive approach, SILS is considered the next major advance in minimally invasive surgical approaches for CRC treatment [30]. However, its use is limited by technical challenges, including loss of triangulation, in-line orientation, and instrument collision, among others, as well as inconclusive long-term oncological outcomes. The skill sets and ergonomic demands of this new method of surgery cannot be directly adapted from CLS experience [31]. Therefore, to ensure the quality of the surgery, surgeons participating in this study must pass a blind review of the surgical videos.

Patients with tumours below the peritoneal reflection will be excluded, as our prior surgical experience showed that SILS treatment is very difficult to complete for these patients and often requires conversions intraoperatively. The slim and narrow pelvic space makes it difficult to expose the surgical field and the surgical instruments collide frequently, resulting in poor mobilization of the low rectum [32]. Jung et al. [33] reported that in 144 SILS low anterior resection (LAR) cases and 3 SILS abdominoperineal resection (APR) cases, an additional trocar was added in 107 patients. They consider SILS plus one additional trocar a second-string procedure during SILS LAR because of its unique complexity and difficulty in achieving distal division with an insufficiently angled stapler and without proper total mesorectal excision. Patients with neoadjuvant treatment will also be excluded, as these patients often develop tissue oedema and fibrosis, making SILS surgery more difficult.

Currently, no RCT has been designed to investigate the long-term oncologic outcomes of SILS for CRC. In addition, it remains controversial whether SILS has the potential benefits of better cosmetic effects and less postoperative pain and whether SILS increases the incidence of incisional hernias. This study is expected to provide relevant high-quality clinical evidence, particularly of the oncologic outcomes of SILS compared to CLS for CRC, and promote its widespread use.

## Data Availability

The datasets generated during the current study will be available from the CSILS Research Committee on reasonable request after the publication of the main findings.

## Abbreviations

AE: Adverse events
AJCC: American Joint Committee on Cancer
APR: Abdominoperineal resection
ASA: The American Society of Anaesthesiologists
BMI: Body mass index
CLS: Conventional laparoscopic surgery
CME: Complete mesocolic excision
CRC: Colorectal cancer
CT: Computed tomography
CTCAE: Common Terminology Criteria for Adverse Events
CRO: Contract research organizations
DFS: Disease-free survival
eCRF: Electronic case report form
ECOG: Eastern Cooperative Oncology Group
EDC: Electronic data capture
EKG: Electrocardiogram
EORTC: European Organization for Research and Treatment of Cancer
IDMC: Independent Data Monitoring Committee
IEC: Independent Ethics Committee
LAR: Low anterior resection
MITT: Modified intent-to-treat
MRI: Magnetic Resonance Imaging
NCCN: National Comprehensive Cancer Network
NOTES: Natural orifice transluminal endoscopic surgery
OS: Overall survival
POD: Postoperative day
PP: Per-protocol
RCT: Randomized controlled trials
SAP: Safety analysis population
SILS: Single-incision laparoscopic surgery
TME: Total mesorectal excision
VAS: Visual analogue scale
